### Strengths and limitations

4.2

The main strength of our approach is the simplicity of the app and the direct integration of ReMindCare into daily clinical practice. As stated before, one of the most important factors regarding the sustainability of e‐health interventions relies upon good integration into the workflow of health systems (Abbott, Foster, Marin Hde, & Dykes, 2014; Appelbaum & Wohl, 2000; Cresswell & Sheikh, 2013; Granja, Janssen, & Johansen, 2018). The ReMindCare app was designed with the main objective of being useful not only for patients but also for health providers. In this regard, the user‐friendly design of the app, its integration into the public hospital workflow and the free access to the app for patients are major strengths that aim to ensure the use of the app by both patients and clinicians and to improve, as a result, the quality of treatment that patients receive and the quality of health services that clinicians provide.

Another main strength of our study is that the development of the app was based on two previous studies (Bonet et al., 2017, 2018), which allowed us to be confident about the theoretical framework of the intervention and to truly address the necessities of the patients. As we found in our study (Bonet et al., 2018), patients claimed improvements in communication with clinicians, which was one of our main objectives when we designed the app.

The graphical display of information can be regarded as another major strength. The integrated graphics provide a quick overview of the health status of the patient, which is extremely useful in the context of a busy public health system (Arango et al., 2018). Specifically, these graphics can help clinicians detect side‐effects of medication that are not usually commented on by patients, such as sexual dysfunctions. This is relevant, as medication side‐effects are one of the most important factors affecting medication dropouts (García et al., 2016).

Finally, the ReMindCare app has been developed in three languages, Spanish, English and Catalan, which allows the use of the app in different countries and autonomous communities.

However, some limitations must be taken into consideration. First, because of the characteristics of this real‐world intervention, our study is not randomized or controlled. However, we plan to compare the main outcomes of the use of the app between users and age‐matched controls, although the groups may differ in some characteristics. Another limitation is that ReMindCare has only been designed for Android systems, although an iOS version of the app is being designed.

To our knowledge, this is one of the earliest e‐health interventions for patients with psychosis implemented as a standard care tool integrated into clinical practice in the public hospital workflow. Real‐time health information is being collected and used to work together with patients to improve the quality of real‐world health care delivery.

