**Methods:**

This is a naturalistic empirical study of patients in a first episode of psychosis programme. The app was purpose‐designed based on two previous studies, and it offers the following assessments: (a) three daily questions regarding anxiety, sadness and irritability; and (b) 18 weekly questions about medication adherence, medication side effects, medication attitudes and prodromal symptoms. The app offers preset alerts, reminders and the ability for patients to reach out to their clinicians. Data captured by the app are linked to the electronic medical record of the patient. Patients will use the app as part of their ongoing care for a maximum period of 5 years, and assessments will occur at baseline and at the end of the first, second and fifth years of app use.

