### Study objectives

2.1

The main objective of this study is to address whether the introduction of the ReMindCare App into daily clinical practice improves the quality of treatment for patients in a first episode of psychosis programme (FEPP).

Specifically, the aims of the study are (1) to assess the effectiveness of the ReMindCare app, in terms of improvement of adherence to anti‐psychotic medication, early detection of relapses and improvement of communication with clinicians, vs treatment as usual in patients with a psychotic disorder; (2) to analyse the use of the ReMindCare app by the patients in terms of rates of adherence, compliance, alerts generated and the total time using the app; and (3) to assess the satisfaction of patients with using the app and the perceived usability of the ReMindCare app.

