### Study design

2.2

In the protocol, we describe the ReMindCare intervention as the first prospective naturalistic and empirical study of an app for FEPP. This app aims to improve the quality of the evaluation and treatment of patients. At the time of submitting this article, ReMindCare had been introduced as a clinical tool into daily psychiatric practice for more than a year. However, enrolment of patients continues, and the first analysis of the data will be conducted by March 2020.

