#### Recruitment and enrolment

2.4.1

Every outpatient from the FEPP who meets the criteria for inclusion is considered a potential user of the ReMindCare app. Once patients enrol in the study, they are able to use the app for a maximum period of 5 years, which is the time when they would be discharged from the FEPP.

All patients interested in using the app must sign an informed consent form and must complete some baseline assessments before their inclusion in the study.

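### The treatment-as-usual comparison matches controls on age only, while outcomes run on an app-use clock that controls do not have, so event counts may cover different risk periods and illness stages

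*Protocol article*

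**What the plan says.** Aim 1 (Study objectives, 2.1) is to assess effectiveness "vs treatment as usual in patients with a psychotic disorder". The only comparator offered for it is in Strengths and limitations (4.2): "we plan to compare the main outcomes of the use of the app between users" and age-matched controls. That section concedes that "our study is not randomized or controlled" and adds the caveat "although the groups may differ in some characteristics".

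On timing, the Abstract places assessments at baseline and "at the end of the first, second and fifth years of app use". Table 1 and section 2.6 use the same scheme, with baseline taken before the patient's own enrolment. Table 1 lists three of the four outcome measures as numbers of events: relapses, urgent care visits and admissions. The fourth is the SMAQ adherence questionnaire.

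On who can be a user, section 2.4.1 says "Every outpatient from the FEPP who meets the criteria for inclusion is considered a potential user of the ReMindCare app", and uptake is by interest: "All patients interested in using the app must sign an informed consent form". Section 2.4.2 admits any illness duration under 5 years. Section 2.2 says "enrolment of patients continues", with a first analysis by March 2020. The Results section gives the launch as October 2018 and 57 patients enrolled. The article does not say where controls come from or how many there are.

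**The concern.** A count of events needs a start and an end. For a user, the app supplies both. For a control, the one stated rule, matching on age, supplies neither, and it does not align calendar time, time in the programme or years of illness. Two patients of the same age can be in the first and the fifth year of illness.

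If controls are eligible patients of the same programme, there is a second difficulty: a control today can be a user next month. Without an alignment rule, a patient's group may then depend on what happened after counting began. A patient who relapses and leaves early can no longer take up the app and stays a control. A patient whose relapse prompts enrolment becomes a user.

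This is distinct from the admitted non-randomisation. It can arise even when the patients in the two groups are otherwise identical, and it affects outcomes taken from hospital records. At stake is whether a user-control difference under Aim 1 can be told apart from a difference in counting windows.

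**Working it through.** The article gives no event rate, uptake rate, drop-out rate or number of controls, so there is no stated figure to reproduce. Everything below assumes an app with **no effect** (true user-to-control ratio 1.00) and shows what unaligned counting can produce. From the article come only the dates, October 2018 to March 2020 (17 months), and the limit of 5 years of illness. All other inputs are assumptions.

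**1. Unequal windows.** If app starts are spread evenly over 17 months, a user has on average 17/2 = 8.5 months from app start to the analysis. A control counted from launch has 17. With equal monthly rates, the ratio of raw counts is 8.5/17 = 0.50. A simulation with a constant monthly chance of uptake (3-8%) and 1% leaving per month is milder, because starts fall earlier and controls also leave. It gives 0.60-0.74, including when nobody leaves because of an event.

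**2. Unequal illness stage.** Suppose controls are counted over their first programme year, and users over one year from an app start spread evenly over programme years 0-4 (mean start 2, so mean mid-window 2.5 years).

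- Straight-line fall from 0.4 to 0.2 events per year over 5 years (slope 0.04): controls 0.4 - 0.04 × 0.5 = 0.38; users 0.4 - 0.04 × 2.5 = 0.30; ratio 0.30/0.38 = 0.79.
- Straight-line fall from 0.6 to 0.2 (slope 0.08): controls 0.56; users 0.40; ratio 0.71.
- Rate 0.4 in year 1 and 0.2 afterwards: only starts in the first year (a quarter of users) overlap year 1, by half a year on average; users 0.2 + 0.2 × 0.5 × 0.25 = 0.225; ratio 0.225/0.4 = 0.56.

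The size depends on the shape of the fall. While rates fall, the direction under this choice of windows does not.

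**3. Group set by later uptake.** These are monthly simulations of identical patients over 17 months. Users are those who took the app by the analysis; controls are those who had not. Events are counted as rates per patient-time, so unequal window length is already removed.

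| Assumption | Users counted from app start | All user time counted |
|---|---|---|
| Uptake unrelated to relapse, constant rate | 0.99-1.01 | 0.99-1.01 |
| 10-50% leave the programme after an event (0.36 events per year, uptake 3-8% per month) | 0.69-0.97 | 0.57-0.93 |
| No uptake for about 3 months after a relapse | 0.85-0.94 | 0.76-0.81 |
| Relapse triples uptake for about 3 months | 1.16-1.38 | 1.35-1.58 |

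In the second row, 5% uptake with 25% leaving after an event gives 0.89 when users are counted from app start. The last two rows assume annual relapse risks of 20-40% and uptake of 3-6% per month.

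**4. After alignment.** Letting patients contribute control time until they take up the app, and user time afterwards, gives 0.99-1.01 in the constant-rate settings above. If the relapse rate is doubled in the first programme year, this step alone leaves 0.90-0.93. Illness stage therefore has to be aligned as well.

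**The case against.** The strongest reply is that the article never says controls are programme patients who had not taken the app by the analysis date. A reader might infer this from open enrolment and from every eligible outpatient being a potential user, but the text does not support it as the only meaning. Patients treated before October 2018, patients without an Android phone, or patients who declined would fit equally well. Pre-launch controls could never have switched groups, and a refusal supplies its own date. This stands: the switching problem in step 3 is conditional on concurrent, eligible controls. It does not remove steps 1 and 2, because historical controls also need a start date placed at a comparable time in the programme.

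A second tempting inference is that the bias must flatter the app. It need not. It disappears when uptake is unrelated to relapse, rates are constant and events are divided by patient-time. It reverses when relapse prompts enrolment.

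Third, a journal article may leave control index dates and switching rules to a fuller document, so their absence alone would be no criticism. That is fair. What remains is the rule the article does state: matching on age, which cannot align outcomes timed by app use.

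Fourth, the magnitudes rest on assumed inputs; in particular, nothing in the article supports 10-50% leaving after an event. That also stands.

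Finally, the article admits that the groups may differ. That caveat concerns who the patients are, not when counting starts.

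**Conclusion.** The point holds in a conditional form. The stated comparison aligns the groups on age alone, while outcomes are timed by app use and users may enter at any illness duration under 5 years. Unless a further rule is applied, record-based event counts can cover different periods and illness stages.

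The size for this study cannot be derived from the article. Under the assumptions shown, a null app gives ratios of 0.60-0.74 for raw counts from unaligned starts, 0.56-0.79 when rates fall from 0.4 to 0.2 per year, and 0.57-1.58 across the settings for later uptake, including settings with no bias. The first range would shrink if users and controls were both held to full one-year windows, but the article states no window for controls. The last range applies only if controls are concurrent patients who could take up the app. The comparison rule should be changed before users and controls are compared; the figures show that the problem can matter, not how large it is here.

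**What to change.** State where controls come from. Then:

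- On each user's app-start date, choose one or more patients who are in the programme and not yet users on that date, matched on age and years of illness. Use that date as the index date for both.
- Count relapses, urgent visits and admissions per patient-month from the index date.
- If a control starts the app, end the control time there and count later time as user time.
- If controls are historical or cannot use the app, place their index date at the same time in the programme as the matched user's app start.

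The cost is a few sentences and some programming with dates that the hospital record should hold for admissions and urgent visits. Some control months are lost when controls take up the app. The pool of not-yet-users may be small, since every eligible outpatient is a potential user and the number of controls is not given. The change does not serve the SMAQ, because nothing in the article shows that questionnaire being collected from non-users at an index date. Nor does it remove differences in who chooses the app, which the article already concedes.

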## Data Availability

The data that support the findings of this study are openly available in [repository name e.g “figshare”] at http://doi.org/[doi], reference number [reference number]
